#### Sample size and power

The study will recruit 60 participants for the randomized trial. Estimating that 15–20% may be lost to follow-up, there will likely be 50 participants with complete parent-adolescent data. We will use these participants to make judgments regarding feasibility and acceptability. Effect size estimates in prior PW studies have ranged from small to very large; the only study conducted among adolescent substance users found small to medium effects, but unlike this application, that study did not offer in-person support or an online parent board (supports that may contribute to larger effect sizes). Furthermore, even small effects, if obtained by delivering content electronically via a highly scalable platform that can reach large numbers of parents, can have significant public health implications. Despite issues with effect size stability in small samples [99], a small to medium effect paired with high levels of feasibility and acceptability would therefore be an indication that the adapted PW intervention should be tested in a larger trial. Based on the detected effect size, post hoc power analyses will be conducted to determine the number of parents required for a fully powered trial. For instance, for power of .8, a small effect size (d = .3) would require a sample of 175 per group, while a medium effect size (d = .5) would require a much smaller sample of 64 per group.

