### Participants

A total of 70 parent-adolescent dyads (10 in Phase 1/open trial and 60 in Phase 2/pilot randomized trial) will be recruited from the acute residential treatment center. To qualify for the study, parents must meet these inclusion criteria: (1) be the parent or legal guardian of an adolescent, aged 12–17 years; (2) had adolescent admitted to residential treatment due to problems related to substance use; (3) will be the primary guardian living with the adolescent immediately post-discharge; (4) willing to receive a parenting intervention; (5) fluent in English or Spanish; and (6) willing to provide written consent and adolescent willing to provide written assent. Adolescents automatically qualify if their parents meet these criteria. The only exclusion criteria are conditions that might preclude the adolescent’s participation in a 2–3 h interview (e.g., mania, psychosis, and cognitive impairment). Based on recent enrollment data, we conservatively expect at least 50% of new admissions to be eligible (with discharge to another facility, discharge to another caregiver, or parent unwilling to receive an intervention as primary reasons for exclusion). To meet our recruitment goal of 70 parent-adolescent dyads, we will need to enroll 25–30% of eligible parents over the first 2 years of the study.

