### Data analysis plan

All 60 parents will be included in statistical analyses consistent with an intent-to-treat (ITT) model. Prior to the main analyses, descriptive statistics will be run on key variables to examine distributional properties, identify outliers, and transform variables as needed. The two treatment conditions will be compared on baseline demographic and clinical variables using basic two-group independent sample t-tests. Using a *p* < .05 criterion, significant pre-existing baseline differences between conditions on any variables will be controlled in subsequent analyses.

GAIN-Q3 data will be entered into the GAIN’s proprietary software, which offers instant error checks and validation reports to prevent missing data. Other forms will be entered directly into study laptops using REDCap (Research Electronic Data Capture), a secure web-based application, to reduce missing data and entry errors. Attrition analyses will compare follow-up completers and non-completers on baseline clinical and demographic variables to determine if they differ systematically. If no systematic differences are found between completers and non-completers, then missing data will be estimated using multiple imputation methods with five datasets, an approach that has been shown to generate unbiased estimates when data are missing at random or missing completely at random [93].

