#### Primary outcomes: feasibility and acceptability

In the open trial and randomized controlled pilot trial, feasibility will be examined via enrollment rates (>80%) and indicators of parental engagement, with the following preliminary targets: attendance of >1 coaching sessions pre-discharge and >1 sessions post-discharge for >75% of parents, and online usage patterns of 2+ PW logins, 2+ parent board logins, and 1+ h logged in for >75% of parents. Criteria for acceptability include withdrawal rates (<20%), satisfaction ratings (>80% of items on the CSQ rated “agree” or “strongly agree”) and positive feedback from exit interviews with parents and therapists. Criteria will be finalized based on parent and staff feedback in Phase 1.

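### The set named for judging the primary feasibility and acceptability outcomes (about 50 dyads with complete data) conflicts with the all-60 intent-to-treat statement and, taken literally, makes the withdrawal criterion unable to fail

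*Protocol article*

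**What the plan says.** Specific aim 1 makes feasibility and acceptability the primary outcomes. The protocol identifies the participants on whom they will be judged in two places.

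- Sample size and power: "The study will recruit 60 participants for the randomized trial". Then: "Estimating that 15–20% may be lost to follow-up, there will likely be 50 participants with complete parent-adolescent data". The next sentence reads: "We will use these participants to make judgments regarding feasibility and acceptability".
- Data analysis plan, opening sentence: "All 60 parents will be included in statistical analyses consistent with an intent-to-treat (ITT) model".

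The section Primary outcomes: feasibility and acceptability sets the criteria. Withdrawal is to be below 20%, and the coaching-attendance and online-usage targets are each to be met by more than 75% of parents. That section does not say which participants form the denominator. Table 3 defines the withdrawal rate as the percentage of parents who withdraw from the study.

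**The concern.** In the Sample size and power section, the natural antecedent of the words used is the group of about 50 with complete parent-adolescent data. Families who withdraw are direct evidence on acceptability, and that group excludes them. Engagement may be affected in the same way, because parents who disengage from the programme may also be the ones who miss follow-up.

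The consequence reaches past the pilot. The same section says that a small to medium effect, paired with high feasibility and acceptability, would indicate that the intervention should be tested in a larger trial. If these rates are computed on completers only, part of that case rests on a set from which contrary evidence has been removed.

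**Working it through.** **Inputs.** 60 randomised; 15–20% lost to follow-up; about 50 complete (Sample size and power). Withdrawal below 20% and engagement targets met by more than 75% of parents (Primary outcomes). The allocation ratio is not stated, so 30 in PW+ is an assumption.

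**1. The plan's own figure.** Complete = 60 × (1 − loss). At 15%, 60 × 0.85 = 51. At 20%, 60 × 0.80 = 48. The stated 50 lies between these and is reproduced.

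**2. Withdrawal.** A parent who withdraws from the study before follow-up ends does not have complete data. Among those with complete data, the number withdrawn is therefore zero.

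| Withdrawn, of 60 | Rate on all 60 | Rate on complete-data set | Under 20%: all 60 / complete-data set |
|---|---|---|---|
| 9 | 15% | 0/51 = 0% | pass / pass |
| 12 | 20% | 0/48 = 0% | fail / pass |
| 15 | 25% | 0/45 = 0% | fail / pass |
| 20 | 33% | 0/40 = 0% | fail / pass |

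The first two rows treat every expected loss as a withdrawal. Loss to follow-up is broader than withdrawal, so 15–20% is an upper bound on the withdrawal the plan implies.

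**3. Engagement, single example.** Assume 30 in PW+, 5 of them lost, and 20 of the 25 completers meeting a target.

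- Completers: 20/25 = 80% (exact 95% CI 59–93%), a pass.
- All 30, none of the five met the target: 20/30 = 67% (47–83%), a fail.
- On all 30, a pass needs 23/30 = 76.7%.

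**4. Engagement, range.** Overall rate = completer rate × (1 − loss) + rate among the lost × loss. With 80% in completers:

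| Rate among the lost | Overall at 15% loss | Overall at 20% loss |
|---|---|---|
| 80% (equal) | 80% | 80% |
| 50% | 75.5% | 74% |
| 20% | 71% | 68% |
| 0% | 68% | 64% |

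The direction and size of any bias depend wholly on how the lost parents engaged. With equal engagement there is none.

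**5. Is the restriction needed?** No. Table 3 measures engagement by sessions attended, logins, time spent and texts viewed. These are process records that exist whether or not a family returns for assessment. Table 2 runs the primary outcomes to 12 weeks and the adolescent assessments to 24 weeks, so a family lost only at 24 weeks can have met every target. A parent who loses custody is not given the parenting measures (Assessments), so that dyad can also fall outside the complete-data group, however engaged the parent was.

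**The case against.** The strongest reply is that this is one loose sentence in a sample-size paragraph. Table 3 defines withdrawal among parents generally, the Data analysis plan includes all 60, and the Primary outcomes section never limits itself to completers. That section also draws on the open trial, calls its engagement targets preliminary and leaves the criteria to be finalised after Phase 1. A rule that makes the withdrawal rate meaningless is more likely a drafting slip than an intention. That is fair as to intent. It does not settle the text: the sentence is the only one that ties a set of participants to feasibility and acceptability by name, and the criteria section gives no denominator that would overrule it.

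A reader might infer more than the documents support:

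- *That 15–20% is the expected withdrawal rate.* The protocol gives it as loss to follow-up.
- *That engagement will be inflated.* The protocol does not say that lost parents engage less. Its background on families who are hard to engage makes this plausible, no more.
- *That including standard-care parents among the 50 adds to the inflation.* They have no access to PW, so counting them would lower the rate. The targets can sensibly apply only to PW+.
- *That the enrollment criterion of over 80% is contradicted by the 25–30% in Participants.* That figure is the share of eligible parents needed to reach 70 dyads and does not forecast acceptance. Table 3 does not restrict the participation rate to eligible parents.
- *That these rates formally trigger a larger trial.* The protocol calls them an indication.

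**Conclusion.** The concern holds as a conflict over the analysis set for the primary outcomes, with one definite consequence and one conditional one.

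- **Definite, if the sentence is followed as written:** withdrawal is about 0% whatever happens, and the criterion carries no information. This assumes only that a parent who withdraws from the study lacks complete data.
- **Conditional:** engagement is overstated if lost PW+ parents engaged less than completers. In the illustration the result moves from 67% to 80%, across the 75% threshold. That rests on an assumed arm of 30, five lost, and none of the five meeting the target.

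The two sections must be reconciled. This goes beyond detail left to a fuller document, because the article states an analysis set and the one it states is unsuitable.

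**What to change.** Reword the sentence in Sample size and power so that it agrees with the Data analysis plan, and name the denominator for each criterion:

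- **Withdrawal:** all 60 randomised dyads, reported by arm.
- **Engagement:** all parents randomised to PW+, using recorded attendance and logged usage whether or not follow-up was completed. Count a parent as not meeting a target only when the records show it. Scoring a parent as a failure merely for missing an assessment would bias the rate downward.
- **Satisfaction (CSQ):** PW+ respondents, with the number missing stated.
- **Precision:** an exact 95% confidence interval for each rate. With about 30 parents these are wide, as 47–83% for 20/30 shows.

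The cost is a change of wording. No new data are needed. The reported rates may turn out somewhat less favourable.

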## Discussion

This protocol evaluates whether a technology-assisted parenting intervention can improve the treatment outcomes of adolescents discharged from acute residential treatment. The approach builds upon qualitative data collection with parents of adolescents in residential treatment and combines both in-person and technology-delivered intervention elements to improve parental engagement at a time when parents have especially poor attendance.

Findings from this protocol will be subject to important limitations. First, the residential program is based in Rhode Island about 15 min from a major urban center. Results of this protocol may not generalize to programs in other states or more rural regions. Second, the PW+ condition and the SC condition do not offer an equivalent dose of contact time. It is therefore possible any favorable results associated with PW+ may be accounted for by a higher “overall” dose of treatment (e.g., coaching sessions, text messages, time spent on the parent message board, time spent completing the computer program). Because this is a treatment development protocol, we focus our resources on developing and pilot testing the experimental condition. If results are promising, we will attempt to control for contact time in a fully powered trial.

By adapting and evaluating an intervention for parents of adolescents in residential treatment, this protocol has the potential to advance treatment by: (1) addressing a high-needs population; (2) targeting parenting skills (putative mediators) that have been shown to influence adolescent substance use and related risk behaviors; (3) working with parents at a critical treatment juncture (i.e., immediately prior to and following the adolescent’s discharge from residential treatment); and (4) developing a model with potential for widespread dissemination in community residential programs. If results of this protocol are promising, future research will attempt to evaluate the PW+ protocol in a fully powered protocol. To accelerate the translation of research to practice, the fully powered trial will use a type 1 hybrid effectiveness-implementation design that simultaneously gathers data on the effectiveness of the model under real-world conditions and collects data on barriers and facilitators to effective implementation [100].

## Abbreviations

CSQ: consumer satisfaction questionnaire
CTRS: Cognitive Therapy Rating Scale
GAIN-Q3: global appraisal of individual needs—quick version
PI: principal investigator
PW: Parenting Wisely
SC: standard care
SUD: substance use disorder
